### Substudies

#### Substudy to assess the acceptability of the intervention

The aim is to gain greater understanding of the impact of the research process and the acceptability of FAST MRI.

Each participant who has consented to stage 2 will be asked for feedback on acceptability relating to the FAST MRI scan via a survey. The survey is detailed in online supplemental material file 2.

Qualitative data collected on the survey will be analysed using qualitative content analysis. The survey will give the participant the option to agree to be contacted to take part in an interview to discuss their answers further. Participants who agree to be contacted for interview will be sent a qualitative study information sheet. Informed consent will be received verbally and audio-recorded at the start of the arranged interview, and the researcher will complete the informed consent form in writing on the participant’s behalf.

Demographic information, including about protected characteristics, will be collected for all participants at the time of the stage 2 consent (to FAST MRI) process. This information, along with results of the analysis of the survey, will be used to purposively select potential participants for the qualitative interviews, to assess the equality and equity impact of the research. If inequalities are identified while this study is ongoing, amendments to process will be investigated and discussed with the steering committee and the PPI panel under the guidance of the study’s PPI leadership team. If deemed feasible, changes may be rolled out following obtaining appropriate approvals.

Semistructured interviews with up to 60 participants will be undertaken. Interviews will be subject to a priori framework analysis using the Theoretical Domains Framework (TDF).^40 41^ The topic guide for the interviews is detailed in online supplemental material file 3.

#### FAST MRI reader substudy

We will report FAST MRI reader outcome data (by professional group, experience and demographics data), diagnostic accuracy of reader groups, time taken to report scans, numbers of scans requiring arbitration, standard arbitration outcomes and expert panel arbitration outcomes.

An additional analysis, for scans classified as MRI 3, will compare expert panel decisions (3a or 3b) versus standard reader opinion (3a or 3b) with scan outcome at study end (cancer/no cancer).

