#### FAST MRI interpretation and display

FAST MRI scans acquired during the study are displayed as maximum intensity projections and stacks of slices in axial and sagittal planes.

FAST MRI readers are both researchers and study participants (FAST MRI reader substudy).

DYAMOND FAST MRI readers must:

Be employed by a participating site.Be a mammogram reader for the NHS Breast Screening Programme.Have completed FAST MRI DYAMOND reader training.^30^,^34^Have credentialed (by interpreting a standardised assessment test set of FAST MRI scans with known outcome and achieving a predefined specificity and sensitivity).^34 35^Have completed Good Clinical Practice (GCP) training and be included on the site delegation log.Be able and willing to provide their informed consent.

FAST MRI readers are trained to classify scans according to the UK 5-point scale^14 36^ (MRI 1: normal; MRI 2: benign; MRI 3: indeterminate/probably benign; MRI 4: suspicious of malignancy; and MRI 5: highly suspicious of malignancy).

The FAST MRI scans will be interpreted by at least two certified FAST MRI DYAMOND readers, with arbitration for disagreement between readers.

The readers will be from a site other than that of the participant whose scan is being interpreted to ensure that they have no access to the participant’s standard care mammogram when interpreting the FAST MRI. This will be achieved using image viewing technology developed by RSNFT (RiViewer).^37^

All MRI 3 results will be reviewed by an expert panel who will additionally classify the scan as 3a or 3b.

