#### FAST MRI results

If a participant’s FAST MRI scan is classified as:

MRI 1 or 2,^36^ the participant and her General Practitioner (GP) will be sent a normal findings confirmation letter.MRI 3a, the participant and GP will be sent a letter telling them that they will be invited for a repeat FAST MRI in 1 year (Y1 FAST MRI scan).MRI 3b, 4 or 5,^36^ the research team will contact the participant by telephone to inform them of an appointment for further investigation.Those found to have a biopsy-confirmed breast cancer (invasive and non-invasive) will be treated as per local practice appropriate for the size, stage and type of cancer detected.Those with no cancer confirmed will be invited for a repeat FAST MRI in 1 year (Y1 FAST MRI scan).

At year 1, scans will be classified into MRI 1/2 (no further action required) or MRI 4/5 with a referral to the assessment clinic. Readers at year 1 will have access to the year 0 scans for reference/comparison.

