## Discussion

Defining the population likely to benefit from an intervention is an essential step in the design of a full effectiveness and cost-effectiveness trial. This study will discover whether screening clients with average breast density could potentially benefit from breast screening with FAST MRI and the results of this study will inform the design and study population of a future RCT to assess FAST MRI’s effectiveness and cost effectiveness as a screening tool for breast cancer within the NHSBSP’s population-risk mammographic screening programme.

The current study will explore QA processes utilising novel, dedicated phantoms and an equipment QA protocol to standardise FAST MRI quality across NHS sites. It will answer uncertainties around feasibility, acceptability, uptake, recall rates and the differential use of imaging modalities needed to guide biopsies indicated by FAST MRI (ultrasound, tomosynthesis and MRI). Evaluation of this study’s novel method of image analysis for uncertain/probably benign results (MRI 3 classifications) will inform the method of image analysis that will be used in the future RCT.

The aim of the FAST MRI research programme (https://www.nbt.nhs.uk/FASTMRI), sponsored by North Bristol NHS Trust, is to investigate whether FAST MRI can cost-effectively detect aggressive cancers earlier than current standard (screening) practice and thereby reduce both breast cancer mortality and the number of people experiencing years of morbidity from living with metastatic breast cancer. The programme has great potential for positive impact. This current study is an important step to define who could benefit from screening with FAST MRI.

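### The expert panel's 3a/3b call decides how each MRI 3 scan is worked up, so an overall panel-versus-reader comparison against outcome at study end can overstate the panel's relative sensitivity

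*Protocol article*

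**What the plan says.** All places are in the protocol article.

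- **FAST MRI interpretation and display:** the panel makes the operative call on every indeterminate scan. "All MRI 3 results will be reviewed by an expert panel who will additionally classify the scan as 3a or 3b".
- **FAST MRI results, 3a:** the participant and GP are told by letter that "they will be invited for a repeat FAST MRI in 1 year (Y1 FAST MRI scan"). No Y0 investigation is described.
- **FAST MRI results, 3b (handled with MRI 4 and 5):** "the research team will contact the participant by telephone to inform them of an appointment for further investigation". After that work-up, "Those with no cancer confirmed will be invited for a repeat FAST MRI in 1 year".
- **FAST MRI results, Y1 rule:** "At year 1, scans will be classified into MRI 1/2 (no further action required) or MRI 4/5 with a referral to the assessment clinic". Y1 readers can see the Y0 scan.
- **Study outcomes:** cancer registry and NBSS (National Breast Screening System) records are reviewed during the study for everyone taking part, whatever the panel decided.
- **FAST MRI reader substudy:** an additional analysis of MRI 3 scans "will compare expert panel decisions (3a or 3b) versus standard reader opinion (3a or 3b) with scan outcome at study end (cancer/no cancer").
- **Discussion:** evaluation of the study's method for MRI 3 scans "will inform the method of image analysis that will be used in the future RCT".

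**The concern.** Two classifications of the same scans are to be set against one outcome, but one of them determines how thoroughly that outcome is ascertained. This is differential verification. It acts through the scans on which panel and reader disagree:

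- **Panel 3b, reader 3a.** The scan is worked up at Y0. A cancer found there counts for the panel and against the reader.
- **Panel 3a, reader 3b.** There is no Y0 work-up. The reader is credited only if the cancer is confirmed through a Y1 scan read as MRI 4/5 or through record review. A cancer not known by study end is scored as a correct 3a for the panel and a false 3b for the reader.

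At stake is the reading method for indeterminate scans in the future RCT, which this evaluation is meant to inform. A panel no more accurate than the readers could appear more sensitive.

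**Working it through.** The article gives no figure for this comparison, so there is nothing of its own to reproduce. It does not state the number of MRI 3 scans, the cancers among them, the accuracy of either call, or confirmation rates. All values for these below are assumptions.

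**1. Direction.** Let u be the probability that a cancer present at Y0 is confirmed by study end after panel 3b, and v the same after panel 3a. The 3b route is the 3a route plus a Y0 assessment. If that assessment finds a fraction a of cancers independently of the later steps, u = 1 − (1 − a)(1 − v), which is never below v. This presumes that a negative Y0 work-up does not make the Y1 scan less complete or less sensitive. On that footing the difference in verification can raise the panel's apparent sensitivity relative to the readers' but not lower it.

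**2. Size, equal true accuracy.** Assume Y0 cancers among MRI 3 scans split 2 (both 3b) : 1 (panel 3b only) : 1 (reader 3b only) : 0.5 (both 3a). True sensitivity is then 3/4.5 = 66.7% for each. Take u = 0.95.

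- Confirmed cancers: D = 0.95 × 3 + v × 1.5
- Apparent panel sensitivity: 0.95 × 3 / D
- Apparent reader sensitivity: (0.95 × 2 + v × 1) / D

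| v | D | Panel | Reader | False gap |
|---|---|---|---|---|
| 0.95 | 4.275 | 2.85/4.275 = 66.7% | 2.85/4.275 = 66.7% | 0 |
| 0.90 | 4.20 | 2.85/4.20 = 67.9% | 2.80/4.20 = 66.7% | 1.2 points |
| 0.70 | 3.90 | 2.85/3.90 = 73.1% | 2.60/3.90 = 66.7% | 6.4 points |
| 0.50 | 3.60 | 2.85/3.60 = 79.2% | 2.40/3.60 = 66.7% | 12.5 points |
| 0.30 | 3.30 | 2.85/3.30 = 86.4% | 2.20/3.30 = 66.7% | 19.7 points |

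Other splits at v = 0.5, in the same order of cells: 1:1:1:1 gives 0.45/2.90 = 15.5 points; 4:1:1:0.5 gives 0.45/5.50 = 8.2; 2:0.5:0.5:0.5 gives 0.225/2.875 = 7.8.

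**3. A second model.** Let panel and reader calls be independent given disease, with u = 1. Apparent panel sensitivity is s/[s + (1 − s)v], where s is its true value; the reader's stays at its true value. With s = 0.70 for both, the panel appears as 0.72, 0.76 and 0.82 at v = 0.90, 0.75 and 0.50. A panel that is truly worse can look better: with s = 0.60 against a reader at 0.70, v = 0.5 gives 0.60/(0.60 + 0.20) = 0.75 against 0.70.

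The effect on specificity is slight. Assume true sensitivity 0.70 and specificity 0.60 for both, 10% cancer among MRI 3 scans and v = 0.5. Scans scored as no cancer are 0.90 + 0.10 × 0.30 × 0.5 = 0.915. The panel appears as 1 − 0.360/0.915 = 0.607. The reader appears as 1 − (0.360 + 0.10 × 0.30 × 0.70 × 0.5)/0.915 = 0.595.

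**4. How complete the Y1 scans could be.** Key study dates gives a first scan on 22 May 2025, 8 months of recruitment (to about 22 January 2026) and grant end on 31 October 2026. Only participants scanned by 31 October 2025 reach one year by grant end: 162 of 245 days, about 66% under uniform accrual. The article does not date study end. If it were the grant end, about 34% of Y1 scans would fall after it, leaving record review alone for those panel 3a scans.

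**5. How many cancers.** At the design's target rate, 0.011 × 959 = 10.5 additional cancers are expected, and these span MRI 3b, 4 and 5 together. If the split in step 2 is read as counts (4.5 MRI 3 cancers), the 12.5-point gap is 2.85 against 2.40 confirmed cancers, a difference of 0.45 of one cancer.

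**The case against.** The strongest reply is that the article gives this analysis one sentence. It names no pooled sensitivity, no test and no claim of superiority, and the data analysis plan expects no formal testing. A panel-by-reader table against outcome would fit the wording, and its layout could be left to an analysis plan that is not shown. This stands in part: the article does not commit to a pooled accuracy figure. It does not dispose of the point, because the comparison, its outcome and the work-up routes are all stated here. An analysis plan could add caveats but could not equalise the work-up.

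It is also fair that chance may well outweigh this bias with so few cancers, and that the 50% confirmation rate has no source. At 90% the example's gap is about 1 point.

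A reader might infer more than the article supports:

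- **That the panel must come out ahead.** It need not. Panel 3b calls without cancer count as false positives, and panel 3a cancers found later count against the panel.
- **That a Y1 read with the Y0 scan to hand measures only change, so stable cancers are missed.** The article does not say how a persistent, unchanged lesion is to be classified. With no category 3 at Y1, it could equally be raised to MRI 4.
- **That the bias persists however complete follow-up is.** It vanishes if Y1 scanning and record review find every Y0 cancer.
- **That this comparison will choose the RCT's reading method.** The Discussion says the wider evaluation will inform it. Recall, biopsy and early call rates, Y1 classifications and panel arbitration outcomes also bear on that choice.

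**Conclusion.** The point holds in a limited form. Because the panel's call sets the work-up, an overall comparison of panel and reader 3a/3b calls against outcome at study end can overstate the panel's relative sensitivity. The direction follows from the stated routes, provided that a negative Y0 work-up does not weaken Y1 ascertainment. The size cannot be derived from the article: it runs from nothing under complete ascertainment to about 12.5 points in the assumed example at 50% confirmation after 3a, and depends on the assumed split and rates. This is a descriptive secondary analysis on very few cancers. The primary outcome and the two-stage decision rule do not depend on it. It is still worth correcting, because the result is meant to inform the future RCT and the correction is cheap.

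**What to change.** In the FAST MRI reader substudy section, and in the analysis plan to match, specify that the MRI 3 comparison is reported by panel decision:

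1. **Panel 3b scans.** Report confirmed cancers and benign recalls by reader opinion (3a or 3b). All these scans are referred for Y0 investigation whichever way the reader called them, so this shows the cancers that the readers' call would have deferred and the benign recalls it would have avoided.
2. **Panel 3a scans.** Report cancers confirmed by the Y1 scan or record review, by reader opinion, labelled a lower bound on the cancers present at Y0.
3. **Interpretation.** State that verification differs between the two groups, and draw no panel-versus-reader accuracy conclusion from the pooled outcome.

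This changes analysis and reporting wording only. It needs no new data, readers or procedures and leaves participants' follow-up as it is. The cost is that the study gives up a single panel-versus-reader accuracy figure.

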#### Central pathology collation of cancers detected

At the time of stage 2 consent, the research nurse will explain to all participants that if they should be recalled for further investigation following their FAST MRI scan, there will be an option for additional tissue analysis and donation. This information is also included in the stage 2 Participant Information Sheet.

A separate Tissue Donation Participant Information Sheet and Consent Form will be offered to those participants recalled for further investigations from their FAST MRI scan. Then, at the assessment clinic, participants will be approached by their clinical team or a member of the research team to ask for consent for a tissue sample to be sent to the University of Birmingham (UoB) for additional analysis and potential donation to the UoB tissue bank.

Participants who consent will donate an additional sample at the time of their percutaneous biopsy. If subsequent routine histological analysis of the biopsy shows it to be a cancer, the additional research sample will be examined to ensure the sample contains cancer tissue and then undergo additional analysis and be stored for future research.

Central review of cancer cases by an expert specialist histopathologist will comprise:

Histological review to confirm type and grade of cancer.Molecular categorisation, for example, luminal, triple negative, HER2 positive cancer.Scoring of tumour-infiltrating lymphocytes (TILs) following the guidelines of the International Immuno-Oncology Working Group.^42^

Should additional funding become available during the study, further analysis will be undertaken to profile the microenvironment.

After all study analysis has been undertaken, if the participant has consented, then the samples will be gifted to the Human Biomaterials Resource Centre at the University of Birmingham for future research.

### Public and patient involvement (PPI)

Our PPI contributors include external patient groups, PPI leadership team and PPI panel as detailed in Box 3 and are a vital and respected part of the FAST MRI Research Team. Our collective PPI contributors’ personal experiences enabled them to guide and question the research team during the planning of the research question and study design.

Box 3Public and patient involvement (PPI)PPI contributors to this studyPPI leadership team: Two PPI lay researchers and one PPI lead/facilitatorExternal patient groups:ICPV: https://www.independentcancerpatientsvoice.org.uk/BUST: https://www.bustbristol.co.uk/UK Breast Cancer Clinical Studies Group: https://breastcancernow.org/sites/default/files/cp_uk_bccsg_position_paper_tor_-_final_mar_2024_1.pdfBreast Density Matters UK: https://www.facebook.com/breastdensitymattersuk/Lobular Breast ancer UK: https://lobularbreastcancer.org.uk/PPI Panel: A dedicated panel (of 6 plus 2 Lay Researchers from the PPI Leadership Team) identified from: individuals having breast screening with mammography and/or MRI and women with lived experience of breast cancerPPI contribution to study designOur PPI contributors guided the design of:Recruitment strategies:Concept of an infographic/visual flyer and posterFirst approach by the clinical team at standard mammogram attendanceDevelopment of a two-stage consent processMethods of results delivery:Positive results to be delivered by telephone—by someone able to answer questions about what the result will mean for the participantNegative results to be delivered by letter/emailMethods to reduce false-positive biopsies:Importance of explaining the results categories to participants at the outset (verbal and written information)PPI contribution to study conductAt study set-up, PPI helped to ensure the study protocol is feasible, inclusive and accessible to study participants. Additionally, the design, accessibility and inclusivity of the participant information, including the formal participant information sheet, was written jointly with the two lay researchers and reviewed by the wider PPI Team.During the study, the PPI team will work with the study’s qualitative researcher to support the analysis and collaborate on the interpretation of the qualitative results to help validate the results and to inform future study design and any changes required for the current study.PPI contribution to study disseminationEvaluation of our results by the public through the external patient organisations within our PPI network will be vital since important questions about the acceptability of levels of cancer detection and of error in screening are likely to be raised.Our PPI contributors will lead public dissemination of the study’s progress and results, ensuring communications, publications and presentations are accessible and engaging.

Our PPI contributors were central to the design of the participant-facing elements of the proposed research. They have highlighted the importance of keeping MRI scan times short and that, for them, the absence of ionising radiation is an important advantage of FAST MRI over mammography. They expressed their appreciation of the fine balance of risk versus benefit in breast cancer screening.

The clinicians and PPI team discussed the literature and estimates of false-positive biopsies from FAST MRI and collaboratively developed the study’s strategy for dealing with MRI 3 (uncertain/probably benign) results, taking into account how these might be interpreted when reported to participants.

Our PPI leadership team have co-produced all participant-facing literature and advertisements.

The PPI group will be involved in the interpretation of the interview data (intervention acceptability substudy) to check research interpretation. PPI members are part of the study management group and trial steering committee. They will be involved in the study conduct and are integral to plans for dissemination of the results (Box 3).

## 
Ethics and dissemination

### Ethical considerations

The study will be conducted according to the UK Policy Framework for Health and Social Care research and to the international standards known as ‘Good Clinical Practice’.

The NHSBSP Research and Innovation Development Advisory Committee approved the protocol on 27 September 2023.

This study was approved by the NHS Health Research Authority (HRA) and Health and Care Research Wales (HCRW) following a favourable ethical opinion being received from Yorkshire and The Humber–Sheffield Research Ethics Committee (REC) on 9 January 2024 (REC reference 23/YH/0268 IRAS 330059).

### Trial oversight

The Trial Management Group (TMG) is responsible for the daily running and management of the study.

The Independent Data Monitoring Committee (IDMEC) is responsible for reviewing and assessing recruitment, interim monitoring of safety and effectiveness, trial conduct and external data, via the IDMEC Report to the Trial Steering Committee (TSC).

The TSC provides advice to the TMG, funder and the Sponsor via the Independent Chair and is responsible for the ultimate decision for the continuation of the study.

### Safety considerations

This trial is categorised as: Type B=Somewhat higher than the risk of standard medical care. The study intervention (FAST MRI) includes the use of gadolinium-based contrast agent (GBCA), which poses a medium level of risk. The risk of GBCA cannot be mitigated; however, safety protocol in relation to adverse events is well documented. The risk and potential adverse impacts from having a FAST MRI scan are detailed in online supplemental material file 4.

### Key study dates

Greenlight for recruitment start: 4 April 2025

Recruitment of first participant (time of first FAST MRI scan): 22 May 2025

Recruitment is anticipated to take 8 months to the recruitment target of 1000 participants.

Grant end date is 31 October 2026.

### Dissemination

Planned publications:

Study protocol (this report).FAST MRI acceptability.Primary outcome.

Results will be published using open access formats in international peer-reviewed scientific journals.

